## Abstract

**Background:**

Smoking cessation improves the health and well-being of people who smoke. It also benefits society, given the high economic and personal costs of smoking-related diseases. With the emergence of new digital technologies, there has been a shift in the delivery of smoking cessation interventions, moving from the traditional in-person treatments to remote digital interventions. In particular, despite a tremendous increase in the number of smoking cessation mobile applications, very few have been empirically tested. Additionally, it remains unclear whether therapeutic contact could improve smoking abstinence outcomes. Therefore, the overall goal of this study is to assess the efficacy of a newly developed app adapted from an in-person efficacious cognitive-behavioral treatment (CBT) for smoking cessation compared to the app in combination with different doses of therapeutic contact.

**Methods:**

We will conduct a randomized controlled trial (RCT) with a sample of 420 individuals seeking smoking cessation treatment at the Smoking and Addictive Disorders Unit of the University of Santiago de Compostela (Spain). Participants will be randomly assigned to: (1) 8 weeks of smoking cessation app (Only app; *n* = 140); (2) 8 weeks of smoking cessation app + 8 weekly sessions of group CBT delivered via video calls (High intensity; *n* = 140); or (3) 8 weeks of smoking cessation app + 4 biweekly sessions of group CBT delivered via video calls (Low intensity; *n* = 140).

**Discussion:**

We expect that the high intensity therapeutic contact group will result in higher 7-day point-prevalence smoking abstinence (validated via carbon monoxide) at the end of treatment and 3-, 6-, and 12-month post-treatment, compared to the other two conditions. This study will be the first RCT evaluating the dose of therapeutic contact needed when using a smoking cessation app. Findings will contribute to improving the efficacy and reach of smoking cessation treatments.

**Trial registration:**

ClinicalTrials.gov number: NCT06900985 registered on March 21, 2025. Protocol version 1.0.

## Background

Smoking is a well-established risk factor for both physical [1] and mental health [2], and remains the leading preventable cause of morbidity and mortality worldwide [3, 4]. In recent decades, significant advances have been made in tobacco control in most countries, including Spain. As a result, the prevalence of smoking has been decreasing progressively over time. However, smoking rates in Spain are still high, with 17% of the adult population smoking daily [5]. This results in high personal and economic costs due to the associated premature mortality and the economic burden at the health care level [6].

Smoking cessation interventions, including cognitive-behavioral approaches [7], have proven to be efficacious to quit smoking [8], but accessibility and utilization of these interventions remain a challenge [9]. Therefore, it is crucial that we develop highly efficacious treatments that can reach a broader population. In recent years, Information and Communication Technologies (ICTs) have become powerful in facilitating communication and information sharing, and, especially, for providing healthcare. The COVID-19 pandemic has further accelerated the development and adoption of these technologies, including video calls for remote interventions targeting a variety of physical (e.g., diabetes, heart failure), and psychological problems (e.g., anxiety, depression) [10, 11]. Studies have shown no differences in mental health treatment outcomes when the same intervention is conducted in person compared to a video call format [12–14]. Additionally, there has been a tremendous proliferation of mobile health (mHealth) apps to deliver a wide variety of clinical interventions [15]. Apps have numerous advantages over in-person treatments. For example, apps can remove geographic and financial barriers to treatment, increasing access to care [16]. Despite the number of advantages that mHealth interventions have, they also have a number of barriers. High rates of dropout and low treatment adherence have been reported as one of the main limitations [17].

In recent years, we have experienced a high increase in the number of smoking cessation mobile apps. However, few have been empirically tested and they have shown limited efficacy for smoking abstinence [18]. In this line, Bricker et al. [19] conducted a randomized controlled trial to test the efficacy of an app (iCanQuit) based on acceptance and commitment therapy, compared with a National Cancer Institute app (QuitGuide) based on US clinical practice guidelines. Findings from this study showed that self-reported 30-day point prevalence abstinence at 12 months post randomization was 28.2% for iCanQuit vs. 21.1% for QuitGuide.

Previous systematic review and meta-analysis suggested that adherence to digital interventions can be improved by incorporating therapeutic contact [20]. Specifically, it seems that self-guided interventions combined with health professional contact before and during treatment improved outcomes compared with no contact [21, 22]. Smoking cessation apps can be used as stand-alone interventions or as combined interventions guided by health professionals, resulting in treatments of varying intensities [23]. Therefore, different levels of intervention dose should be established, ranging from self-guided interventions (such as using Apps) to those conducted by professionals following a stepped-care approach [24, 25]. However, research examining the effect of in-person contact of varied intensity from a professional on digital interventions for substance use has been scarce. Eék et al. [26] and Sundström et al. [27] conducted a randomized controlled trial in a sample of participants with alcohol use disorder, examining the efficacy of a therapist-guided high‐intensity internet intervention (web-based) compared with an unguided low‐intensity internet intervention. No significant differences were found between conditions in the short [27] and the long term [26], suggesting that low-intensity internet interventions may be at least as efficient as high-intensity ones.

Considering the relevance of smoking cessation treatment reach and the impact of treatment adherence on cessation outcomes, examining the role of therapeutic contact in digital interventions to quit smoking is warranted. The aim of this study is to assess the efficacy of a smoking cessation app compared to the same app in combination with different doses of therapeutic contact (high vs. low) via a randomized controlled trial (RCT). Secondary aims include the assessment of treatment adherence, participant satisfaction, and potential moderators (e.g., age, education) and mediators (e.g., depression, withdrawal symptoms).

## Methods

### Study design

The study includes two phases. The aim of the first phase is to design the app prototype by a multidisciplinary team composed of psychologists and telecommunication and computer engineers. We used a qualitative research approach, conducting in-depth individual interviews with the target population to understand their preferences for smoking cessation apps, potential barriers to use, and general feedback on how to make the app more attractive. In the second phase, we will conduct a three-arm, RCT to assess the efficacy of the app compared to different doses of therapeutic contact (high vs. low) (Fig. 1). This protocol is consistent with SPIRIT (Standard Protocol Items: Recommendations for Interventional Trials) guidelines [28].

**Fig. 1 Fig1:**
[figure not shown]
Study design overview: App development and RCT. *Note*. HITC: High Intensity Therapeutic Contact (*n* = 140); LITC: Low Intensity Therapeutic Contact (*n* = 140); Only App (*n* = 140)

### Participants and study procedures

Participants in both phases 1 and 2, will be individuals seeking smoking cessation treatment at the Smoking and Addictive Disorders Unit of the University of Santiago de Compostela (Spain). Recruitment will be conducted via social media, press communications, flyers, health care referrals or by word of mouth. Potential participants will contact the Unit staff by telephone or email. Prior to enrollment, they will be scheduled for an eligibility assessment session through videoconference. To be part of the study, participants will meet the following inclusion criteria: age 18 or over; interested in receiving smoking cessation treatment; provide electronic informed consent; smoking at least 5 cigarettes per day; completion of all pre-treatment assessment questionnaires; having a valid email address; having a smartphone; and being willing to use it throughout the treatment. We will exclude individuals with a diagnosis of a severe mental disorder (e.g., bipolar disorder and/or psychotic disorder) or with a concurrent substance use disorder (e.g., alcohol, cannabis); We will also exclude those reporting concurrent use of other tobacco products (electronic cigarette with nicotine, cigars or cigarillos) or who have completed an efficacious psychological or a pharmacological treatment to quit smoking during the previous year (e.g., nicotine replacement therapy). Individuals who recently had a physical pathology involving high vital risk that requires immediate intervention (e.g., recent myocardial infarction) will also be excluded. Finally, individuals with visual difficulties that prevent the use of the app will also be excluded from the study.

Interested individuals meeting the inclusion criteria will then sign the electronic informed consent form. Participants in Phase 2 (RCT) will complete the baseline assessment through an individual interview, lasting approximately one hour, and via the Microsoft Teams video-calling platform. Afterwards, a link will be sent for the completion of the baseline questionnaires through Microsoft Forms. Post-treatment assessments will be conducted electronically at the end of treatment and at 3-, 6-, and 12-months follow-ups in the three treatment conditions (see Fig. 2).

### Procedures

#### Phase 1: app design

To inform the design of the app, we will conduct semi-structured in-depth individual interviews via Microsoft Teams. Before data collection, an interview guide will be developed, with key topics (e.g., previous experiences with apps and smoking cessation apps, perceived utility of apps, facilitators and barriers to using apps, app content for smoking cessation, opinions on the initial app prototype) drawn from the literature to ensure alignment with existing research. These interviews will be recorded and transcribed verbatim. Each interview will last approximately 30 to 45 min. The information collected from the interviews will be used to design and refine the app. The participants in Phase 1 will not be included in Phase 2.

Then, a beta test will be conducted to assess users’ experience with the app and determine acceptability and ease of use. For this purpose, we will recruit a convenience sample of experts (i.e., health professionals) and potential users (i.e., people who smoke). Participants in this beta test will have access to the app prototype for a period of two weeks. Then, an individual interview will be conducted by the research team to gather information that will be used to refine the app and create a final version.

#### Phase 2: randomized controlled trial

##### Randomization, allocation concealment and blinding

In phase 2, participants who meet all the eligibility criteria will be randomized to one of the three groups based on a computer-generated allocation sequence (ratio: 1.1.1). Participants will not be blinded to the treatment condition, which is common in trials evaluating psychological and psychosocial interventions due to the intervention characteristics [29].

##### Treatment conditions

Participants will be randomly assigned to one of three treatment conditions. All three conditions will have the same smoking cessation app, but they will differ in the dose of therapeutic contact (high, low, or no contact), in terms of number of sessions (8 vs. 4 vs. 0) and frequency (weekly vs. biweekly vs. no contact). Additionally, the high-intensity therapeutic contact condition involves the systematic introduction and practice of multiple behavioral and cognitive techniques by a trained therapist, whereas the low-intensity therapeutic contact condition relies more on the use of the app with the therapist providing support related to progress review, problem-solving, and reinforcement of key intervention components (e.g., smoking reduction goals).

All study participants will be followed 3-, 6-, and 12-month post-treatment.

*App content*:

Participants will have access to our smoking cessation app during their participation in the study (14 months total duration of app access). The app content is based on an evidence-based cognitive-behavioral treatment “*Programa para Dejar de Fumar*” [30, 31]. The intervention components are digitally adapted via personalization, tracking (e.g., setting physical activity goals based on baseline activity level), motivational support (e.g., having in mind that the benefits of quitting smoking are higher than the negative consequences) and achievement goals reinforcement through push notifications (e.g., You have achieved the 100% of your weekly goal!) and gamification (i.e., a badge system for abstinence goals achievement). These features are intended to increase engagement, reinforce progress, and support adherence to smoking-reduction and abstinence goals.

The program includes the following components that are delivered over the course of 8 weeks: (1) information about the app; (2) tracking the number of cigarettes smoked per day; (3) psychoeducation on tobacco and smoking; (4) nicotine fading through weekly cigarette reduction goals (30% reduction every week from first treatment week) including a personalized quit day (estimated on the fifth or sixth treatment week); (5) stimulus control by selecting daily situations in which they will progressively stop smoking (e.g., driving); (6) coping with urges to smoke and withdrawal syndrome; (7) weekly physical activity goals tailored to individuals baseline level; (8) social support; (9) anhedonia and mood-focused behavioral activation tasks; (10) smoking relapse prevention; 11) motivational notifications; and 12) a reward system for goal achievement (gamification). In addition to all the previous components, during the follow-up period participants will also have access to the following components: (1) strategies for coping with craving and motivational strategies; (2) gains and achievements after quitting; (3) tips for maintaining abstinence or quitting smoking; (4) possibility of tracking cigarette use and setting a new quit date.

Although our app shares components with other evidence-based apps, such as push notifications, badges, tracking the number of cigarettes smoked per day, or gains and achievements after quitting, it differs from existing smoking cessation apps in several app-specific features. Whereas the present app operationalizes a structured CBT smoking cessation program with evidence in Spain [32], with several digitally adapted features, particularly personalized nicotine-fading goals, individualized physical activity goals, behavioral activation exercises, among others, previous existing apps include components based on other framework, such as Acceptance and Commitment Therapy (i.e., iCanQuit) [33], mindfulness (Cravingtoquit) [34], or US clinical practice guidelines (i.e., QuitGuide; QuitSTART) [35]. Additionally, the app is designed to be used as a standalone app but also to be combined with standardized professional support.

*Treatment conditions (TC)*:

*Only App.*

Participants will have access to the smoking cessation app, with no therapeutic support (technical support will be provided if necessary).

*App + High-intensity therapeutic contact.*

Participants will receive 8 one-hour weekly group sessions via the Microsoft Teams video-calling platform, and they will have access to the app. All sessions will be conducted by clinical psychology/general health psychology professionals. The app components we previously described will be discussed in depth during the 8-week online sessions. Participants will have access to the topics discussed during session within the app.

*App + low-intensity therapeutic contact.*

Participants in this condition will receive four one-hour sessions applied in a group format every two weeks via the Microsoft Teams video-calling platform and will have access to the app. The four sessions will have the following content: (1) explanation of treatment rationale and components available in the app; (2) participants’ progress monitoring, reinforcement of achieved goals, and analysis of difficulties; (3) cessation planning support; and (4) relapse prevention support. The sessions will be conducted by clinical psychology/general health psychology professionals.

### Sample size calculation

We expect to reach theoretical saturation after interviewing 30 participants in Phase 1 to discuss app design and beta testing [36]. However, we will conduct additional interviews if new information continues to emerge.

To determine the sample size for the RCT (Phase 2), the statistical program G* power [37, 38] was used. We estimate a 20-percentage point difference in smoking abstinence between the treatment conditions with therapeutic contact at the 12-month follow-up (estimated percentages of 45% for High-intensity and 25% for Low-intensity). This estimate was based on a previous study in which the higher abstinence rate of a condition with 8 sessions and an App reached the 42.6% of 7-day PPA at 12-month follow-up [39]. Therefore, we hypothesize that 45% of participants in the High-intensity condition will be abstinent, as the intervention in the present study includes additional components compared with our previous study (i.e., tailored physical activity, social support, and anhedonia- and mood-focused behavioral activation tasks). Given that the Low-intensity condition comprises fewer therapist-guided sessions, we conservatively estimated approximately a 50% lower abstinence rate at the 12-month follow-up compared with the High-intensity condition. Therefore, assuming a 20-percentage point difference in abstinence outcomes between the High-intensity and Low-intensity conditions, a two-sided α of 0.05, and 90% power, the required sample size was 120 participants per group. We anticipate a 15% loss to follow-up based on our previous research, so we increased the per-group sample size to 140 participants. Consequently, the total sample size required for the study is 420 participants.

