#### Phase 2: RCT

All statistical analysis will be conducted following an intention-to-treat approach [76] in which all randomized participants will be included in the final analysis. Sociodemographic (e.g., age, sex, gender, education), tobacco-related and clinical characteristics will be reported via descriptive statistics. Parametric (χ^2^ and Student’s t) and non-parametric test (Mann-Whitney U) will be used to examine baseline differences between treatment conditions in sociodemographic variables, tobacco use, clinical variables and variables related to the use of mobile phones and apps. Given that our treatment conditions that include therapeutic contact are delivered in a group format, the primary analysis will account for clustering by treatment/contact group. The pattern of missing data will be analyzed, and multiple imputation techniques will be used based on the missingness pattern.

To analyze differences between treatment conditions, percentages of smoking abstinence (χ^2^) and effect size calculation (Cramer’s V) will be used. Due to the longitudinal nature of the collected data, statistical analyses regarding smoking abstinence outcomes will be conducted through multilevel modeling.

Moderation analysis will be conducted to examine whether treatment effects differ as a function of participant baseline characteristics, such as nicotine dependence, age, or education level. These analyses will test whether the intervention has different abstinence outcomes for specific subgroups by including treatment-condition × baseline characteristic interaction terms in the longitudinal multilevel models. We will also explore which variables could act as mechanisms of change via mediation models. Mediators will include negative affect, withdrawal symptoms, and self-efficacy.

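### The 90% power for High vs Low intensity was derived for independent participants, although both arms are treated in groups and the primary analysis will account for that clustering

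*Protocol article*

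**What the plan says.** Under Sample size calculation, the protocol article uses "estimated percentages of 45% for High-intensity and 25% for Low-intensity" and concludes that with "a two-sided α of 0.05, and 90% power, the required sample size was 120 participants per group". The only inflation is for attrition: "We anticipate a 15% loss to follow-up based on our previous research, so we increased the per-group sample size to 140 participants". That gives 420 in total. The section names no group size, number of groups, ICC or design effect.

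Under Treatment conditions, both contact arms meet in groups by video call. High intensity has eight weekly group sessions. For Low intensity, "Participants in this condition will receive four one-hour sessions applied in a group format every two weeks". Only App has no contact groups.

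Under Statistical analysis, Phase 2: RCT, the article says that "the primary analysis will account for clustering by treatment/contact group". The same section keeps every randomised participant in the analysis. It also names a chi-square comparison with Cramér's V, and multilevel modelling for the longitudinal abstinence data. Under Primary outcome, people lost to follow-up are counted as smoking.

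**The concern.** The analysis section recognises that outcomes within a contact group may be correlated, and the sample size section does not. The powered contrast is between exactly the two arms treated in groups, so any positive correlation inflates the variance on both sides of it. The 90% is the only power figure in the article, and High vs Low is the central dose question. If the real power is nearer 75% to 85%, a non-significant difference is weaker evidence that fewer sessions suffice than a nominal 90% would suggest.

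**Working it through.** **Inputs from the article:** p1 = 0.45, p2 = 0.25, two-sided α = 0.05, power 0.90, 120 evaluable and 140 randomised per arm, 15% loss.

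**Inputs assumed, because the article does not give them:** group size m = 6 to 10 and ICC = 0.01 to 0.05. Both are taken as equal in the two arms, with equal group sizes and no small-sample correction for the number of groups.

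**Step 1. Reproduce the plan's figure.**

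n = [z(0.975)·√(2·p̄·(1−p̄)) + z(0.90)·√(p1(1−p1) + p2(1−p2))]² / (p1−p2)², with p̄ = 0.35

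= [1.960·√0.455 + 1.2816·√0.435]² / 0.20² = [1.322 + 0.845]² / 0.04 = 117.4, so 118 per group.

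The arcsine version gives 117.2, also 118. The stated 120 is therefore the independent-participant figure, slightly rounded up. The room left in it is 120/117.4 = 1.02, so no meaningful design effect is hidden there. For attrition, 120/0.85 = 141.2 and 120 × 1.15 = 138. The stated 140 is consistent with an attrition allowance alone.

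**Step 2. Add clustering.** Design effect DE = 1 + (m−1)·ICC, and effective n = n/DE in each of the two arms.

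- Smallest: m = 6, ICC 0.01, DE = 1 + 5 × 0.01 = 1.05, and 120/1.05 = 114.
- Largest: m = 10, ICC 0.05, DE = 1 + 9 × 0.05 = 1.45, and 120/1.45 = 83.

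**Step 3. Power under three readings**, from Φ{[(p1−p2)·√(n/DE) − z(0.975)·√(2·p̄·(1−p̄))] / √(p1(1−p1) + p2(1−p2))}:

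- A: 120 evaluable per arm, 45% vs 25%.
- B: all 140 analysed, and 45%/25% already count losses as smoking.
- C: all 140 analysed, and 45%/25% are rates among those followed. Counting 15% as smoking gives 0.45 × 0.85 = 38.25% vs 0.25 × 0.85 = 21.25%.

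| m | ICC | DE | A | B | C |
|---|---|---|---|---|---|
| any | 0 | 1.00 | 0.906 | 0.943 | 0.879 |
| 6 | 0.01 | 1.05 | 0.892 | 0.933 | 0.863 |
| 8 | 0.02 | 1.14 | 0.866 | 0.912 | 0.834 |
| 10 | 0.02 | 1.18 | 0.854 | 0.903 | 0.821 |
| 6 | 0.05 | 1.25 | 0.833 | 0.886 | 0.799 |
| 8 | 0.05 | 1.35 | 0.804 | 0.861 | 0.767 |
| 10 | 0.05 | 1.45 | 0.775 | 0.835 | 0.737 |

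**Step 4. What the 140 can absorb under reading B.** 140/117.4 = 1.19. Power stays at or above 0.90 up to that design effect, which means an ICC of about 0.19/5 = 0.038 at m = 6, 0.19/7 = 0.027 at m = 8, and 0.19/9 = 0.021 at m = 10.

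**The case against.** The strongest reply is that 120 is not the number analysed. Losses are counted as smoking and everyone randomised is included, so 140 per arm enter the primary comparison. If 45% and 25% already count losses as smoking, the 20 extra per arm act as a reserve. Power is then 0.943 before clustering and stays at or above 0.90 for a design effect up to about 1.19. This stands as far as it goes. It does not rescue the stated calculation, because the article assigns those 20 to attrition and does not say on which basis the two rates were set. Even on this reading, an ICC of 0.05 takes power below 0.90 at each group size considered.

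Three stronger readings are tempting and are not supported:

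- A reader might infer that any positive ICC breaks the 90%. Reading B contradicts this, and even 120 per arm carries about 2% of room.
- A reader might infer that 90% holds only at ICC = 0. Under reading B it holds well above zero. Under reading C it does not hold even at zero (0.879).
- A reader might infer that the power figure belongs to an analysis the trial will not run. The statistical section does name a chi-square comparison. What the figure does not match is the commitment that the primary analysis accounts for clustering.

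It is also fair to say that the size of the loss rests on assumed inputs. In reading C, the fall from 0.906 to 0.879 comes from attrition and not from clustering. Under reading A, if m is the planned group size, attrition also shrinks the analysed groups and softens the loss a little.

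**Conclusion.** The point holds in this form: the 120 per group and 90% power are correct arithmetic for independent participants, but they were not derived for a primary analysis that accounts for contact-group clustering in both compared arms. For groups of 6 to 10 and an ICC of 0.01 to 0.05, power is 0.89 to 0.78 at 120 evaluable per arm. At 140 analysed it is 0.93 to 0.84 if the rates already count losses as smoking, and 0.86 to 0.74 if they do not. The loss may be negligible or material. The article does not give the group size, the ICC or the basis of the rates, and these decide which.

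**What to change.** Keep 420 participants and amend the Sample size calculation section:

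1. Say that the 120 per group and 90% power assumed no clustering.
2. State the planned contact-group size and an ICC range, for example 0.01 to 0.05.
3. State whether 45% and 25% already count people lost to follow-up as smoking.
4. Restate the High vs Low power for the clustered analysis of 140 per arm over that range.
5. If power is also given for comparisons with Only App, apply the design effect to the contact arm only.

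Do not write that 90% holds only at ICC = 0, since that is wrong on either basis for the rates when 140 per arm are analysed. The cost is a short rewrite and, for much of the range, a less favourable power figure. No extra participants are needed, and nothing changes in treatment or in the planned analysis.
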